#### Clinical outcomes

A member of the research team, who is a qualified health professional, will conduct a skin examination of the participants where moisture resulting from incontinence is likely to occur (buttocks region). This skin examination will determine the prevalence and severity of IAD indicated by the appearance of erythema, erosion, maceration and the presence of IAD pain. Participants will also be asked about their satisfaction with care and their mental health. These data will be collected at the start of the feasibility cluster RCT, at 3 months and at 6 months using the following outcome measures:

Ghent Global IAD Categorization Tool (GLOBIAD).^33^Minimum Data Set (MDS) for IAD.^2^Incontinence-Associated Dermatitis Intervention Tool (to enable assessment of darker skin tones).^34^Wong-Baker FACES Pain Rating Scale.^35^The Short Assessment Patient Satisfaction (SAPS).^36^Hospital Anxiety and Depression Scale (requested by PPI panel to include of assessment of psychological impacts of IAD)^37^

Care staff from all six study sites will also use the MDS for IAD to collect weekly data from the recruited adults living in care homes and their own homes. Therefore, the MDS will be completed on a single day concurrently but independently by a clinical member of the research team (at baseline, 3 months and 6 months) and the recruited care staff (weekly) across all study sites to assess the prevalence and severity of IAD if present. The quantitative data from these data collection tools will be collected using the online survey tool: https://www.onlinesurveys.ac.uk/, which is UK general data protection regulation (GDPR) compliant and certified to ISO 27001 standard. See onlinesupplemental files 3^ 4^.

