Alongside continence promotion and appropriate use of pads and appliances,^13 14^ effective prevention and treatment includes skin cleansing and application of skin protectants.^1 15 16^ Skin protectant products comprise different formulations and ingredients such as petrolatum, zinc oxide, dimethicone or other film-forming molecules.^1 17^ Cleansers contain surface active agents, which help to dissolve the fat-soluble components in water.^18^ The odds of developing IAD if preventative measures are used are almost half (46%) the odds if they are not^11^ and when skincare regimes are implemented, costs might be reduced.^19 20^ The products and procedures for both prevention and treatment are similar^1 17^ and there are numerous options on the market, including prescription and ‘over the counter’ products. However, there is a lack of high-quality clinical trials meaning recommendations are based on low-quality evidence and expert opinion.^21^ Clear guidance is not easily available and public involvement has told us that the use of skin protectants in care homes is variable.

Although skin health can be improved using tailored and evidence-based skincare routines,^9^ nurses find it difficult to differentiate between IAD and other conditions such as pressure ulcers.^22 23^ Nurses are, however, knowledgeable about how IAD is caused but less able to diagnose and make evidence-based prevention and treatment decisions.^24 25^ Nurses’ ability to recognise IAD has been shown to improve through training,^23^ indicating the importance of continuous professional development for the prevention and treatment of IAD. Educational interventions to improve nurses’ management of IAD have taken place largely in hospital settings^24 26 27^ but are lacking in the community where the prevalence is high and unregistered care workers and informal carers provide skincare as well as registered nurses.

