#### Intervention content

The IAD manual is an online, interactive, educational tool with asynchronous written, audio and pictorial content. The intervention includes an illustrated flowchart with six interconnected boxes; clicking on each box reveals evidence-based content about experiences of and preventing and managing IAD. A brief overview of the content of each box and corresponding learning objectives are shown in table 1. There is also a survey at the end of the IAD manual with questions based on the content of and experience of using the IAD manual. Care staff will be emailed a certificate on completion of the questions indicating which ones they answered correctly and incorrectly. They can repeat the self-test questions if they want to improve their score. Researchers will conduct a training need analysis of care staff to identify the starting point of staff knowledge about IAD. Ten care staff at each site will be trained on preventing and treating IAD following the guidelines in the IAD manual. These staff will act as the IAD champions at each site who will be asked to subsequently support their colleagues through the e-learning. The training will be face to face or online and will take up to 4 hours per member of staff. Completion of the manual will go towards staff’s continuing professional development. A training log will be used record staff attendance, number of sessions and duration of each training session by study site.

**Table 1 T1:** Content of the intervention

Box titles	Learning outcomes
1. Improving knowledge about IAD	Describe what incontinence-associated dermatitis (IAD) is and who is most at risk Explain some of the common causes of incontinence of pee and/or poo Describe how incontinence of pee and/or poo affects people and their families
2. Assessment and management of incontinence and promoting continence	Describe what should happen when a person with incontinence of pee or poo is assessed by a nurse Explain how to take samples of pee or poo if asked Explain how to support a person to follow a toileting programme Explain what to do and what not to do when using incontinence pads
3. Steps to prevent skin damage	Describe which skin cleansers to use and which not to use Describe which products can be left on the skin to protect against IAD
4. Identifying IAD	Describe what changes are seen in the skin when IAD develops Explain how to assess the skin when cleansing or changing continence products.

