**Clinical outcomes**						
Ghent Global IAD Categorization Tool		x		X	X	
Minimum Data Set (MDS) for IAD		x		X	X	
Incontinence-Associated Dermatitis Intervention Tool		x		X	X	
Wong-Baker FACES Pain Rating Scale		x		X	X	
The Short Assessment Patient Satisfaction		x		X	x	
Hospital Anxiety and Depression Scale		x		X	x	
Care staff completion of MDS				Once a week for 24 weeks		

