### Pilot outcome analysis

The analysis of GLOBIAD and MDS, Wong-Baker FACES Pain Rating Scale will estimate proportions of patients and 95% CI. The outcomes measured using the Incontinence-Associated Dermatitis Intervention Tool, the SAPS questionnaire, the Hospital Anxiety and Depression Scale will be presented as mean and SD for each treatment group. The analysis will be carried out on the trial population using an intention to treat analysis. Completeness of the data and indication of difference will be assessed to inform selection of feasible clinical outcomes for a definitive trial. There will be no imputation to deal with missing data.

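### After allocation, weekly staff-recorded IAD is open to detection that differs by arm, and the plan neither separates staff from researcher ratings nor uses the same-day pairs that would show it

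*Protocol article*

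**What the plan says.** All references are to the protocol article; the SAP is not shown.

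- **Who records.** Under *Clinical outcomes*: "Care staff from all six study sites will also use the MDS for IAD to collect weekly data from the recruited adults". Table 2 gives the frequency as "Once a week for 24 weeks". The section on randomisation and blinding says that site staff cannot be blinded.
- **A second, paired rating.** At baseline, 3 and 6 months a qualified health professional from the research team examines the skin, and this examination is said to determine prevalence and severity. In addition, "the MDS will be completed on a single day concurrently but independently by a clinical member of the research team" and by care staff. Both ratings are given the same purpose: "across all study sites to assess the prevalence and severity of IAD if present".
- **Who is taught what.** Box 4 of the manual (Table 1) has the learning outcome "Describe what changes are seen in the skin when IAD develops". *Control sites* says that control staff get no extra training and no access to the manual. *Training staff for data collection* and *Payment* give ten staff at each of the six sites 2 hours of data-collection training.
- **What training does.** *Background* says of nurses: "ability to recognise IAD has been shown to improve through training".
- **Analysis and use.** *Pilot outcome analysis*: "The analysis of GLOBIAD and MDS, Wong-Baker FACES Pain Rating Scale will estimate proportions of patients and 95% CI". Completeness and an indication of difference then inform the choice of definitive outcomes. *Prevalence and incidence* feeds prevalence and incidence into the definitive sample size. Neither section names the rater or compares the two.

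**The concern.** The intervention may change the measuring instrument in one arm. Staff who learn to identify IAD may record cases that they would otherwise have missed, or stop recording other skin damage as IAD. If staff MDS supplies the by-arm figures after baseline, the contrast combines any effect on the skin with any effect on recognition. Better case-finding could look like harm or hide a benefit; fewer false positives could look like a benefit.

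No hypothesis is tested, so what is at stake is the design of the next trial. The stated basis for choosing outcomes is completeness plus an indication of difference, and the only numerical threshold for staff-collected outcomes is 70% completion. Staff MDS could meet both while its accuracy differed by arm, and a distorted event rate could enter the definitive sample size.

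**Working it through.** **The plan's own figures.** The article gives no sensitivity, specificity or agreement figure. Its one precision figure, about ±7% for recruitment and retention, is not in dispute and reproduces: 1.96 × √(0.5 × 0.5 / 180) = 7.3 points, and 1.96 × √(0.8 × 0.2 / 144) = 6.5 points.

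**Inputs.** From the article: IAD prevalence 30%; 48 participants per site, three sites per arm; 24 weekly staff ratings; paired ratings at three visits. Assumed, because the article gives none: staff sensitivity (Se) 0.90 in the intervention arm and 0.60 to 0.80 in the control arm; specificity (Sp) 0.95 in both arms unless stated.

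**Formula.** Recorded prevalence = π × Se + (1 − π) × (1 − Sp), where π is true prevalence.

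**1. No true effect, π = 0.30 in both arms, equal specificity.** Intervention: 0.30 × 0.90 + 0.70 × 0.05 = 30.5%.

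| Control Se | Control recorded | Spurious gap |
|---|---|---|
| 0.80 | 27.5% | +3.0 points |
| 0.70 | 24.5% | +6.0 points |
| 0.60 | 21.5% | +9.0 points |

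Participants all have incontinence, and the article expects 30 people with IAD among 58 with incontinence per 100 beds, about 52%. At that prevalence the same rows give +5.2 to +15.6 points.

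**2. Specificity improves too (0.97 against 0.93), Se 0.90 against 0.80.**
- π = 0.30: 0.270 + 0.021 = 29.1% against 0.240 + 0.049 = 28.9%, a gap of +0.2 points.
- π = 0.20: 0.180 + 0.024 = 20.4% against 0.160 + 0.056 = 21.6%, a gap of −1.2 points.

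**3. A true fall from 30% to 20%, equal specificity 0.95.** Intervention: 0.20 × 0.90 + 0.80 × 0.05 = 22.0%. Against control Se of 0.80, 0.70 and 0.60 the recorded difference is −5.5, −2.5 and +0.5 points, where the truth is −10.

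**4. Weekly incidence.** Repeated rating makes specificity matter more. For a person who never has IAD, the chance of at least one false record in 24 weeks is 1 − Sp^24 if weekly errors are independent: 21.4% at Sp 0.99 and 51.9% at Sp 0.97. Errors on one person are likely to be correlated, so these are extremes; with fully repeated errors the figures would be 1% and 3%. Here better specificity with the manual would look like benefit.

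**5. What the pairs can show.** 48 × 3 = 144 pairs per arm per visit, and 288 × 3 = 864 in all, with complete data. At 30% prevalence, 144 × 0.30 = 43.2 people per arm have IAD. The 95% half-width for staff sensitivity is 1.96 × √(0.9 × 0.1 / 43.2) = 8.9 points at Se 0.9 and 1.96 × √(0.6 × 0.4 / 43.2) = 14.6 points at Se 0.6, before any allowance for clustering.

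**The case against.** The strongest reply is that the plan already holds most of the remedy. The researcher examination is said to determine prevalence and severity, GLOBIAD is among the measures collected at those visits, and staff MDS is an addition. An agreement statistic may sit in the SAP, and leaving it out of an article is no error in itself. All of this stands. What remains is that the article gives both sources of MDS the same purpose, reports MDS without naming the rater, and sets out how outcomes will be chosen in terms that do not separate detection from effect.

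A reader might also infer more than the text supports:

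- *Only intervention staff are trained to recognise IAD.* Control staff also get data-collection training, and Table 2 lists MDS training without limiting it to one arm. Its content on recognition is not stated. Only the manual's teaching is confined to one arm.
- *Staff-recorded figures will differ by arm through detection alone.* Step 2 shows that the gap can be close to zero or negative. *Background* says that nurses confuse IAD with pressure ulcers, which is as much a matter of specificity as of sensitivity. Its evidence on training concerns nurses, while the raters here include care assistants.
- *The researcher ratings have no planned use.* They do; only the paired comparison has none stated.
- *The feasibility thresholds are biased.* The 10% prevalence threshold is measured before the intervention, and the 70% staff threshold concerns completion. Manual training begins at allocation, so baseline prevalence is not affected by this route either.

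**Conclusion.** The point holds as a risk after baseline, of unknown size and sign. The article supports each link: unblinded staff as weekly raters, teaching on identification in one arm only, training said to improve recognition, and MDS results used for outcome choice and sample size with no distinction between raters. It does not show that a detection gap will occur.

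Under the assumed accuracies, detection alone moves the staff-recorded contrast by +3 to +9 points at 30% prevalence with equal specificity, and by about −1 to +16 points across the wider set. A true 10-point fall could appear as anything from −5.5 to +0.5. These figures illustrate; none is an estimate from the trial.

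This is an inexpensive improvement worth making. It does not invalidate the feasibility trial, which tests no hypothesis and has a second rater in place.

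**What to change.** - Name the rater for every MDS-based figure. Base by-arm prevalence after baseline, and incidence among those free of IAD at baseline, on the researcher examination.
- Report staff-researcher agreement on the same-day pairs by arm at baseline, 3 and 6 months: kappa, and staff sensitivity and specificity against the researcher, with confidence intervals.
- Show weekly staff-recorded incidence as supportive.
- Add this agreement to completeness and indication of difference when judging whether staff MDS suits the definitive trial.

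The cost is a few lines of analysis on data already planned. Three limits should be stated. Examinations 3 months apart miss short episodes, so both sources should be shown. The researchers who collect data are themselves unblinded and so are an imperfect reference. Per-arm sensitivity is imprecise, about 9 to 15 points either side per visit before clustering, with three clusters per arm. Agreement should therefore be read descriptively and not used as a strict pass or fail rule.

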### Training staff for data collection

Ten care staff at each study site will be provided with training on data collection from the research team. Researchers will enquire if the care staff already have experience of inputting data into online systems such as incident reports. This will enable researchers to pitch the training according to level(s) of staff digital literacy. Care staff will collect the data on IAD using either the paper versions or online survey tool. See schedule of activities in table 2.

**Table 2 T2:** Schedule of enrolment, measurement time points, interventions, assessments and variables

	Enrolment	Baseline	Allocation	Week 12	Week 24	Post
Eligibility	X					
Informed consent	X					
**Randomisation and allocation**			x			
**Participant characteristics**						
Demographic variables (age, sex, ethnicity)		x		x	x	
Care setting		x		x	x	
**Clinical outcomes**						
Ghent Global IAD Categorization Tool		x		X	X	
Minimum Data Set (MDS) for IAD		x		X	X	
Incontinence-Associated Dermatitis Intervention Tool		x		X	X	
Wong-Baker FACES Pain Rating Scale		x		X	X	
The Short Assessment Patient Satisfaction		x		X	x	
Hospital Anxiety and Depression Scale		x		X	x	
Care staff completion of MDS				Once a week for 24 weeks		
**Feasibility outcomes**						
Recruitment and retention rates (cluster and individual)		x		x	X	
Attrition		x		x	x	
Intervention fidelity (non-participant observations of skincare)				x	X	
Completion of data collection (by staff)				x	x	
Acceptability of the intervention (interviews with clients and staff)						X
**Interventions and study-related procedures**						
Training of staff to complete the minimum data set		X	X			
Training of staff in the intervention site only in the IAD manual			X			

IADincontinence‐associated dermatitisMDSMinimum Data Set

### Data analysis

Quantitative data will be sent to the trial statistician for data cleaning. The data will be extracted in csv format and will be imported into Stata or R statistical package for data analysis. The baseline characteristics and outcome data will be described by treatment arm using descriptive statistics. No significance testing will be carried out.

### Feasibility outcome analysis

The analysis will estimate rates and proportions relating to each of the feasibility outcomes, recruitment and attrition rate, of the study. The proportions will be produced alongside the 95% CI for that proportion and the raw count which those proportions are based on. The recruitment of participants over time will be presented in a plot (number or participants vs time). The recruitment into the trial will be summarised in a Consolidated Standards of Reporting Trials diagram.^38^

### Pilot outcome analysis

The analysis of GLOBIAD and MDS, Wong-Baker FACES Pain Rating Scale will estimate proportions of patients and 95% CI. The outcomes measured using the Incontinence-Associated Dermatitis Intervention Tool, the SAPS questionnaire, the Hospital Anxiety and Depression Scale will be presented as mean and SD for each treatment group. The analysis will be carried out on the trial population using an intention to treat analysis. Completeness of the data and indication of difference will be assessed to inform selection of feasible clinical outcomes for a definitive trial. There will be no imputation to deal with missing data.

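### Clinical outcomes are summarised as unadjusted arm values, although baseline values are collected and an informal arm comparison will help choose the definitive trial's outcomes

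*Protocol article*

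**What the plan says.** All references are to the protocol article.

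- **Collection.** The Clinical outcomes section lists six tools completed by the research team and says "These data will be collected at the start of the feasibility cluster RCT, at 3 months and at 6 months using the following outcome measures". Table 2 marks all six at baseline, week 12 and week 24. The separate staff-completed MDS is scheduled "Once a week for 24 weeks" and has no baseline mark.
- **General analysis.** Under Data analysis, "The baseline characteristics and outcome data will be described by treatment arm using descriptive statistics", and "No significance testing will be carried out".
- **Outcome summaries.** Under Pilot outcome analysis, "The analysis of GLOBIAD and MDS, Wong-Baker FACES Pain Rating Scale will estimate proportions of patients and 95% CI". For the IAD Intervention Tool, SAPS and HADS, the sentence ends "the Hospital Anxiety and Depression Scale will be presented as mean and SD for each treatment group". No baseline-adjusted, paired or site-level summary of these outcomes is named. Analysis is by intention to treat, and missing data are not imputed.
- **Use of the comparison.** The same section adds: "Completeness of the data and indication of difference will be assessed to inform selection of feasible clinical outcomes for a definitive trial".
- **Design.** Each arm has two care homes and one home care agency, with allocation stratified by that setting type. The Sample size section plans 48 participants per site.

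**The concern.** The analysis is descriptive, but the plan still intends to look at how the arms differ and to let that look help decide which outcomes go forward. The summaries named for this purpose are raw values by arm.

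With three sites per arm, site-to-site variation alone can separate the arms at baseline. Part of such a gap persists at follow-up and could be read as a sign that an outcome responds to the manual, or could hide that it does. The baseline values that would allow for this are already collected.

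A second, smaller point follows from the lack of imputation. The people behind a 6-month mean need not be those behind the baseline mean, so an arm's mean can shift although no one has changed. What is at stake is the choice of outcomes and one planning input for the definitive trial. No conclusion of this trial depends on it.

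**Working it through.** **The plan's own figure.** The only precision figure is the margin of about ±7% for recruitment and retention. It reproduces: 1.96 × √(0.5 × 0.5 / 180) = 7.3 points, and 1.96 × √(0.8 × 0.2 / 144) = 6.5 points. It does not concern the clinical outcomes and is not disputed.

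**Inputs.** From the article: 3 sites per arm, 48 participants per site (144 per arm), and 30 people with IAD among 58 with incontinence per 100 beds (0.517). Assumed, because the article gives no values: ICC 0.01 to 0.10, site-level correlation over time 0.5 to 0.8, and individual-level correlation 0.5 to 0.7.

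**Step 1: chance baseline gap between arms.** In SD units, SE = √(2 × DE / 144), with DE = 1 + 47 × ICC. The 95% range is ±1.96 × SE.

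| ICC | DE | SE (SD units) | 95% range (SD) | 95% range, proportion near 50% |
|---|---|---|---|---|
| 0.02 | 1.94 | 0.164 | ±0.32 | ±16 points |
| 0.05 | 3.35 | 0.216 | ±0.42 | ±21 points |
| 0.10 | 5.70 | 0.281 | ±0.55 | ±28 points |

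The last column multiplies by √(0.5 × 0.5) = 0.5. It suits this trial, since 30/58 is close to one half. The formula ignores stratification by setting type. The Abstract's total of 248 would give about 41 per site; the SE at ICC 0.05 is then 0.221, so the result hardly depends on which size applies.

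**Step 2: how much of a gap persists.** The expected carry-over is the correlation between site means over time: r = [ICC × r_site + (1 − ICC) × r_ind / 48] / [ICC + (1 − ICC) / 48]. Over the assumed ranges it runs from 0.50 to 0.78. At ICC 0.05 it is 0.50 to 0.77, so a gap at the edge of the 95% range (0.42 SD) would leave about 0.42 × 0.50 = 0.21 to 0.42 × 0.77 = 0.32 SD in the raw follow-up contrast with no intervention effect.

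**Step 3: which summary is least noisy.** SE of the follow-up contrast at ICC 0.05:

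- raw values: 0.216
- plain change score: 0.146 to 0.216
- baseline-adjusted, 0.216 × √(1 − r²): 0.137 to 0.187

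A plain change score gains nothing over raw values when both correlations are 0.5. The adjusted figures treat the slope on baseline as known, which is somewhat favourable with six sites.

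**Step 4: planning value of the correlation.** Take an assumed effect of 0.3 SD, two-sided 5%, 90% power, before any design effect. The unadjusted n per arm is 234.

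| r | Baseline-adjusted, factor 1 − r² | Change score, factor 2(1 − r) |
|---|---|---|
| 0.3 | 213 | 327 |
| 0.5 | 176 | 234 |
| 0.7 | 120 | 141 |

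**Step 5: changing denominators (invented figures).** If an arm has mean 8 and the 25% who leave averaged 11, the remaining mean is (8 − 0.25 × 11) / 0.75 = 7.0 with no one having changed. Showing both visits in the same people exposes this shift.

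**The case against.** The strongest reply is that this is a feasibility trial described in a journal article. Its primary objectives are recruitment, retention, acceptability and fidelity, no testing is planned, and paired tables are often left to an SAP, which is not at hand. The outcome section names a type of summary per tool and does not exclude others. This stands in large part and is why the point is minor. It does not dispose of it, because the article itself states both the raw summaries and the decision that the comparison will inform.

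Some stronger readings are tempting but not supported:

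- *A baseline imbalance would be hidden.* It would not. Baseline and outcome data are both described by arm, and one feasibility threshold uses each site's IAD prevalence before the intervention. A visible gap is still not accounted for in the comparison.
- *The data on change that the definitive trial needs will not exist.* The Prevalence and incidence section plans the incidence and SD of IAD, and incidence depends on earlier status. The repeated measures are stored, so a correlation can be derived later. The sample sizes in Step 4 assume a continuous, baseline-adjusted primary outcome, which the article does not propose.
- *Every clinical measure has a baseline.* The weekly staff MDS has no baseline mark in Table 2; the six researcher-collected tools do.
- *Pairing would deal with dropout.* It removes the shift in who is counted, but selective loss of frailer people still affects those who remain.

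Stratification by setting type is also a fair point. If much of the site variation lies between homes and agencies, the ranges in Step 1 are too wide. Differences between individual homes, and between the two agencies, remain.

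**Conclusion.** The point holds as a minor, optional improvement. The named summaries leave the collected baseline values out of a comparison that will inform outcome selection. With three sites per arm, a chance baseline gap of about ±0.32 to ±0.55 SD (95% range) is plausible, and half to about three quarters of it would be expected to carry into raw follow-up values.

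These figures rest on assumed ICCs of 0.02 to 0.10 and assumed correlations over time, with 48 per site and no allowance for stratification. They show how large the problem could be and do not predict it. Nothing here biases a stated conclusion of the trial, since no test or formal effect estimate is planned.

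**What to change.** Add to Pilot outcome analysis:

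1. For the six researcher-collected tools, in participants with both values, report baseline and follow-up side by side by arm and by site at 3 and 6 months, with the number contributing.
2. For the scored measures, report the baseline-to-follow-up correlation as a planning input.
3. Read any apparent difference between arms from baseline-adjusted values, not from raw follow-up values or plain change scores, and present it descriptively without a significance test.

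The cost is a sentence or two of text and a little programming; no new data are needed. There are small downsides. The paired tables cover only participants with both values, which does not remove bias from selective dropout, and adjusted contrasts from six sites will be imprecise and should be labelled so.
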